## Abstract

Gait impairments negatively affect the quality of life of people with Parkinson’s disease (PwPD). Aerobic exercise (AE) is an alternative to alleviate these impairments and its combination with transcranial direct current stimulation (tDCS) has demonstrated synergistic effects. However, the effect of multitarget tDCS application (i.e., motor, and prefrontal cortices simultaneously) combined with physical exercise on gait impairments is still little known. Thus, the proposed randomized clinical trial will verify the acute effects of AE combined with tDCS applied on motor and prefrontal cortices separately and simultaneously on gait (spatial-temporal and cortical activity parameters) in PwPD. Twenty-four PwPD in Hoehn & Yahr stages I-III will be recruited for this crossover study. PwPD will practice AE on treadmill simultaneously with the application of anodal tDCS during four intervention sessions on different days (∼ one week of interval). Active tDCS will be applied to the primary motor cortex, prefrontal cortex, and both areas simultaneously (multitarget), with an intensity of 2 mA for 20 min. For sham, the stimulation will remain at 2 mA for 10 s. The AE will last a total of 30 min, consisting of warm-up, main part (20 min with application of tDCS), and recovery. Exercise intensity will be controlled by heart rate. Spatial-temporal and cortical activity parameters will be acquired before and after each session during overground walking, walking with obstacle avoidance, and walking with a cognitive dual task at self-preferred velocity. An accelerometer will be positioned on the fifth lumbar vertebra to obtain the spatial-temporal parameters (i.e., step length, duration, velocity, and swing phase duration). Prefrontal cortex activity will be recorded from a portable functional near-infrared spectroscopy system and oxygenated and deoxygenated hemoglobin concentrations will be analyzed. Two-way ANOVAs with repeated measures for stimulation and moment will be performed. The findings of the study may contribute to improving gait in PwPD. Trial registration: Brazilian Clinical Trials Registry (RBR-738zkp7).

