tDCS has been suggested as a potential clinical tool to improve gait deficits in PwPD [24, 25]. Some authors have demonstrated benefits resulting from the isolated application of tDCS during walking [26–28], while other studies have reported no positive effects [29–32]. Furthermore, a recent meta-analysis indicated that applying tDCS alone does not lead to improvements in short-term motor symptoms of PwPD, including walking [33]. There is a body of evidence suggesting that combining tDCS with physical exercise can promote greater synergistic effects compared to interventions applied separately [34]. In a previous study, the combination of physical training focused on gait and balance with tDCS applied to the primary motor cortex (M1) resulted in a greater increase in gait velocity than either stimulation or exercise alone [22]. In contrast, a single session of AE on the treadmill improved gait velocity and stride length, but these positive effects were not enhanced by tDCS application over the M1 [35]. Indeed, Conceição and colleagues [23] applied AE on a stationary bike with tDCS over PFC and demonstrated a decrease in step time variability, along with an increase in PFC activity in the stimulated hemisphere during walking. This last result suggests that combining tDCS with AE may enhance the utilization of prefrontal resources in gait control, facilitating the compensatory mechanism (greater use of the indirect locomotor pathway) [16]. However, the combined effect of simultaneous stimulation of M1 and PFC with AE has not been tested yet. Stimulating both brain areas may be beneficial, as M1 is associated with the execution of voluntary movements [36] and is hypoactive in PwPD, while PFC acts as a compensatory mechanism for gait control [16].

Given the promising positive effects of stimulating the M1 and PFC during AE, this randomized clinical trial protocol aims to investigate the acute effects of tDCS applied to different target areas combined with AE on the treadmill on spatial-temporal and cortical activity parameters during overground walking, walking with obstacle avoidance and walking with cognitive dual-task in PwPD.

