## Materials and method

### Study design and setting

A randomized, crossover, double-blind, sham-controlled clinical trial will be conducted at the Posture and Gait Studies Laboratory (LEPLO) of São Paulo State University (Unesp), Institute of Biosciences, Rio Claro. This study protocol adheres to the Standard Protocol Items: Recommendations for Interventional Trials (SPIRIT) checklist (S1 Checklist) [37]. The project was approved by the research ethics committee of the same University (CAAE: 54476421.1.0000.5465) and is registered on the Brazilian Clinical Trials Registry platform (RBR-738zkp7) with the Universal Trial Number (UTN) code U1111–1277-3248. Other documents on ethical appraisal can be found in the supporting information (S1–S4 Files). PwDP will visit the laboratory for non-consecutive five days, with screening assessments and treadmill familiarization conducted during the first visit. During the remaining four visits (minimum of one week apart), participants will undergo pre- and post-assessments (gait and cortical activity) and a session of AE combined with anodal tDCS (applied on M1, PFC, multitarget, or sham condition). All experimental procedures will be performed at the same time of the day for each PwPD and during the ON state of Parkinson’s disease medication. Fig 1 shows a SPIRIT diagram for the timeline of procedures.

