### Statistical analysis

Statistical analysis will be conducted using SPSS 25.0 software (International Business Machines Corporation, Armonk, New York, USA), with a significance level set at *p* < 0.05. Clinical, cognitive, and demographic characteristics will be summarized using means and standard deviations or medians and quartiles (25–75) based on the normality of data distribution. The side effects of tDCS will be analyzed with Friedman’s ANOVA. Means and standard deviations will be calculated for primary, second, and intervention outcomes (treadmill velocity and total distance covered, SPE, and percentage of HRmax). Two-way ANOVA with repeated measures for stimulation (M1 x multitarget x PFC x sham) and moment (pre and post) will be employed to analyze gait parameters and activity cortical in each walking condition separately (usual, obstacle avoidance, and dual task). The Mauchly test will be used to check sphericity, and the Greenhouse-Geisser correction will be adopted if necessary. In the case of interaction between factors, Bonferroni post hoc tests with adjusted significance levels will be utilized to identify differences. Finally, for each combination of AE and tDCS, the Standardized Response Mean will be calculated as the effect size of the intervention, considering the mean difference between moments (post—pre) divided by the standard deviation of change.

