## Discussion

This study outlines a randomized clinical trial protocol designed to examine the acute effects of AE on a treadmill combined with tDCS on spatial-temporal gait parameters and PFC activity in PwPD. Our protocol includes gaits assessments in various contexts, including usual walking, walking with obstacles, and performing a cognitive task while walking. This comprehensive approach allows us to gain a better understanding of the immediate effects of the combined intervention on the gait of PwPD. Additionally, we will compare the effects of different tDCS setups in combination with physical exercise, with a particular emphasis on multitarget stimulation.

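### All four sessions contain the exercise, so only what tDCS adds to it is controlled; the pre-post effect size and the moment main effect should not be presented as the effect of the combined intervention

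*Protocol article*

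**What the plan says.** The aim is worded in three places. The Abstract says the study "will verify the acute effects of AE combined with tDCS applied on motor and prefrontal cortices separately and simultaneously on gait". The Discussion describes a protocol "designed to examine the acute effects of AE on a treadmill combined with tDCS on spatial-temporal gait parameters" and expects a better understanding of the "immediate effects of the combined intervention on the gait of PwPD". The Introduction says it "aims to investigate the acute effects of tDCS applied to different target areas combined with AE on the treadmill", which makes tDCS by target the object and exercise the background.

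On design, the Abstract says "PwPD will practice AE on treadmill simultaneously with the application of anodal tDCS during four intervention sessions", and Study design and setting describes each visit as "a session of AE combined with anodal tDCS (applied on M1, PFC, multitarget, or sham condition". No visit without exercise is described.

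On analysis, the Statistical analysis section says "Two-way ANOVA with repeated measures for stimulation (M1 x multitarget x PFC x sham) and moment (pre and post) will be employed", with Bonferroni post hoc tests if the two factors interact. It then defines, for each pairing of exercise and stimulation, an SRM (mean post-minus-pre change over the SD of change) and gives it the role of the intervention's effect size.

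**The concern.** Stimulation type is the only factor that is randomised. Exercise is constant, so no contrast between sessions estimates the effect of exercise or of the whole package. Any statement about the package has to come from change between pre and post, either as the moment main effect or as the within-condition SRM. Both mix any effect of the session with whatever else happens between the two assessments.

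The SRM is the concrete problem. It is a planned output, it has no comparator, and the plan gives it the intervention's name. If the trial found a pre-post change with no stimulation x moment interaction, four positive SRMs could be presented as the effect sizes of four effective interventions when part or all of each was ordinary within-visit change.

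**Working it through.** **1. What each planned quantity estimates**

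For session s, let the mean post-minus-pre change be E + T_s + D. E is the acute effect of the exercise bout. T_s is what stimulation s adds to it, set to zero for sham. D is change that would occur without exercise or stimulation.

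| Quantity | Expected value | Controlled? |
|---|---|---|
| Active minus sham difference in change | T_s | Yes, D and E cancel |
| Moment main effect (mean of four changes) | E + D + mean of T_s | No |
| SRM for one condition | (E + T_s + D) / SD of change, apart from small-sample bias | No |

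With no exercise effect and no tDCS effect, the SRM estimates D in SD units and nothing else.

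**2. What D contains**

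Gait and cortical activity while walking sets three trials in each of three walking conditions, in the same order of conditions before and after. The second assessment thus repeats nine trials. Between the two lie tDCS preparation and a 30-minute exercise protocol, so time since the medication dose differs. Testing in the ON state at the same time of day standardises visits against each other but does not equalise pre with post inside a visit. Counterbalancing the order of sessions does not remove a change that recurs in each of them. Fatigue or warm-up caused by the treadmill bout belongs to E, not to D.

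**3. How often the moment test would be significant with E = T_s = 0**

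The documents give no figure for D, so this is an illustration under stated assumptions.

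- n = 24 (number invited) and n = 16 (stated minimum), both from Sample recruitment and selection, taken as completers. The point does not depend on how the 16 was derived.
- Two-sided alpha 0.05, from Statistical analysis.
- Drift d = 0.1 to 0.4 SD of the single-session change (assumption).
- Correlation r between sessions in the change scores, 0 to 0.5 (assumption).

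The moment test is a one-sample t test on each participant's mean of four changes. In units of the single-session SD of change:

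SD of the mean = sqrt((1 + 3r)/4), and noncentrality = d x sqrt(n) / SD of the mean, with n − 1 degrees of freedom.

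For n = 24, d = 0.1, r = 0.5: SD = sqrt(2.5/4) = 0.791; noncentrality = 0.1 x 4.899 / 0.791 = 0.62; critical t = 2.069; rejection probability 0.09.

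For n = 24, d = 0.4, r = 0: SD = 0.5; noncentrality = 0.4 x 4.899 / 0.5 = 3.92; rejection probability 0.96.

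| Drift (SD of change) | n = 24, r = 0.5 to r = 0 | n = 16, r = 0.5 to r = 0 |
|---|---|---|
| 0.1 | 9% to 16% | 8% to 12% |
| 0.2 | 22% to 47% | 16% to 32% |
| 0.3 | 43% to 80% | 30% to 61% |
| 0.4 | 66% to 96% | 47% to 85% |

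A simulation of the four changes per participant (10,000 runs per setting) agrees: at d = 0.3, r = 0.3, n = 24 it gives 53%.

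**4. The controlled test under the same drift**

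In that simulation the stimulation x moment test was significant in 4.3% to 5.5% of runs, over drifts of 0 to 0.5 SD, correlations of 0 to 0.6 and both sample sizes. A drift common to all sessions does not disturb it.

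**The case against.** **The wording can be read as one question.** The Abstract sentence varies only the stimulation target, the Introduction also describes tDCS combined with exercise, the design is called sham-controlled, and the same Discussion paragraph ends by promising a comparison of tDCS set-ups. Read together, these can mean: which target, given with exercise, against sham with exercise. This largely stands for the Abstract. It stands less well for the Discussion's phrase about the combined intervention, and it does not explain why the effect size for each combination is a pre-post change without reference to sham.

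**No text credits a moment effect to exercise.** A reader might infer that the trial will report a significant moment effect as a benefit of exercise or of the combination. The protocol does not say so, and the only post hoc tests it specifies follow an interaction. The Introduction does describe a cited single-session treadmill study as showing a gait gain that tDCS did not enhance, but that is a literature summary, not an analysis rule. Whether that study had a control for its exercise claim cannot be seen here.

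**The drift is assumed.** This stands. Practice may improve gait and other influences may worsen it, so the net drift could be near zero or negative. The rates above are two-sided, and under a negative drift they would describe apparent worsening. Practice could also fade over visits, so the drift need not be the same in every session.

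**The randomised comparison is intact.** This stands in full. A reader might infer that the lack of a session without exercise undermines the trial. It does not: the comparison with sham plus exercise validly answers the Introduction's aim.

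**Conclusion.** The point holds in limited form. The design controls what tDCS at each target adds to exercise and nothing wider. The plan oversteps this in the SRM, an uncontrolled change given the name of the intervention's effect, and in the Discussion's description of the aim. The Abstract is open to the same reading. Because a named output is affected, this is more than a detail left to a fuller plan.

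The size cannot be fixed from the documents. Over the assumed ranges, the chance of a significant moment effect with no true effect runs from about 9% to 96% with 24 completers and from about 8% to 85% with 16. The low end is as compatible with the protocol as the high end. The correction is worth making but does not threaten the main comparison.

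**What to change.** - **Abstract and Discussion:** state the aim as in the Introduction, made explicit: the acute effect of tDCS at each target, added to aerobic exercise, relative to sham plus the same exercise.
- **Statistical analysis, conclusions:** rest them on the stimulation x moment contrasts of each active condition against sham.
- **Statistical analysis, effect size:** report the active-minus-sham difference in change with its confidence interval, standardised if wanted. Keep the within-condition SRMs and the moment main effect only as descriptive, uncontrolled pre-post change.

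This is a change of wording and of the reported summary. It needs no new session, participant or measurement. The cost is that the trial gives up a causal claim about exercise or the whole combination; only a session without exercise could support one.

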## Introduction

More than six million people are affected by Parkinson’s disease nowadays [1]. Parkinson’s disease is characterized by the progressive loss of dopaminergic neurons in the substantia nigra pars compacta of the basal ganglia [2, 3]. The lack of dopamine causes an imbalance in the inhibitory and excitatory signals sent via the thalamus from the basal ganglia to subcortical and cortical areas (such as the motor cortex). In short, there is an increase in inhibitory signals (GABAergic) from the basal ganglia to the thalamus, and consequently, the thalamus presents an underactive excitatory signal (glutamatergic activity) to the motor cortex, generating hypoactivation of this region [2, 3]. Because of this imbalance, people with Parkinson’s disease (PwPD) may experience rigidity, bradykinesia, resting tremors, postural instability, and impaired walking.

PwPD shows reduced gait velocity, stride length, and swing phase, besides the increase of double support time [4] and gait variability [5] during overground walking compared to neurologically healthy individuals, reducing gait automaticity [6]. Similar gait impairments were also reported during walking with obstacle avoidance [7–9] and with cognitive dual task in PwPD [10, 11]. In addition, changes in cortical activity, measured using functional near-infrared spectroscopy (fNIRS), during walking were reported in previous studies [11–14]. PwPD showed increased activity in the prefrontal cortex (PFC) during overground walking [13, 14], walking with obstacles [13, 15] and walking with cognitive dual task [11, 12] compared to neurologically healthy individuals. The increased recruitment of the prefrontal area can be considered a compensatory neural activity to deal with gait impairments and cortico-basal ganglia impaired pathways [16]. In addition to levodopa-based treatment, incorporating physical exercise can enhance the gait of PwPD.

Aerobic exercise (AE), particularly when performed on a treadmill, has shown promising results in enhancing gait parameters. For example, Pohl and colleagues [17] demonstrated improvements in gait velocity, stride length, and double support time after a single session of AE compared to traditional gait training. Multiple AE sessions have also shown positive effects on gait parameters in PwPD [18–20]. In addition to the behavioral effects of walking, treadmill exercise may increase corticomotor excitability in PwPD [21]. There is evidence that combining physical exercise, including AE, with transcranial direct current stimulation (tDCS) could have even more positive effects on spatial-temporal and cortical activity parameters during walking [22, 23].

tDCS has been suggested as a potential clinical tool to improve gait deficits in PwPD [24, 25]. Some authors have demonstrated benefits resulting from the isolated application of tDCS during walking [26–28], while other studies have reported no positive effects [29–32]. Furthermore, a recent meta-analysis indicated that applying tDCS alone does not lead to improvements in short-term motor symptoms of PwPD, including walking [33]. There is a body of evidence suggesting that combining tDCS with physical exercise can promote greater synergistic effects compared to interventions applied separately [34]. In a previous study, the combination of physical training focused on gait and balance with tDCS applied to the primary motor cortex (M1) resulted in a greater increase in gait velocity than either stimulation or exercise alone [22]. In contrast, a single session of AE on the treadmill improved gait velocity and stride length, but these positive effects were not enhanced by tDCS application over the M1 [35]. Indeed, Conceição and colleagues [23] applied AE on a stationary bike with tDCS over PFC and demonstrated a decrease in step time variability, along with an increase in PFC activity in the stimulated hemisphere during walking. This last result suggests that combining tDCS with AE may enhance the utilization of prefrontal resources in gait control, facilitating the compensatory mechanism (greater use of the indirect locomotor pathway) [16]. However, the combined effect of simultaneous stimulation of M1 and PFC with AE has not been tested yet. Stimulating both brain areas may be beneficial, as M1 is associated with the execution of voluntary movements [36] and is hypoactive in PwPD, while PFC acts as a compensatory mechanism for gait control [16].

Given the promising positive effects of stimulating the M1 and PFC during AE, this randomized clinical trial protocol aims to investigate the acute effects of tDCS applied to different target areas combined with AE on the treadmill on spatial-temporal and cortical activity parameters during overground walking, walking with obstacle avoidance and walking with cognitive dual-task in PwPD.

## Materials and method

### Study design and setting

A randomized, crossover, double-blind, sham-controlled clinical trial will be conducted at the Posture and Gait Studies Laboratory (LEPLO) of São Paulo State University (Unesp), Institute of Biosciences, Rio Claro. This study protocol adheres to the Standard Protocol Items: Recommendations for Interventional Trials (SPIRIT) checklist (S1 Checklist) [37]. The project was approved by the research ethics committee of the same University (CAAE: 54476421.1.0000.5465) and is registered on the Brazilian Clinical Trials Registry platform (RBR-738zkp7) with the Universal Trial Number (UTN) code U1111–1277-3248. Other documents on ethical appraisal can be found in the supporting information (S1–S4 Files). PwDP will visit the laboratory for non-consecutive five days, with screening assessments and treadmill familiarization conducted during the first visit. During the remaining four visits (minimum of one week apart), participants will undergo pre- and post-assessments (gait and cortical activity) and a session of AE combined with anodal tDCS (applied on M1, PFC, multitarget, or sham condition). All experimental procedures will be performed at the same time of the day for each PwPD and during the ON state of Parkinson’s disease medication. Fig 1 shows a SPIRIT diagram for the timeline of procedures.

**Fig 1 pone.0300243.g001:**
[figure not shown]
SPIRIT diagram of enrollment, interventions, and assessments.

### Participants

#### Sample recruitment and selection

This study will employ the convenience sampling technique, selecting, and recruiting PwPD from the community-dwelling. The sample size was calculated in G*Power software version 3.1, based on data from Fernandez-Lago colleagues [35]. The primary outcome and statistical tests used were gait velocity and Two-way ANOVAs with repeated measures (within factors), respectively (alpha = 0.05; beta = 0.08; ηp^2^ = 0.43). The sample size analysis indicates a minimum of 16 PwPD is required for this study. Considering the potential for sample loss, we will invite 24 PwPD to participate in the clinical trial through personal and/or telephone contact (from November 10^th^, 2023, to March 31^st^, 2024). In case we have a positive reply, a member of the research team will explain the study’s objectives, risks, benefits, and ethical implications. If participants consent to participate in the study, they will be asked to sign two copies of an informed consent form (one for themselves and the other for the member of the research team).

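### The planning effect (partial eta squared 0.43) comes from a study in which, by the protocol's own account, tDCS added nothing, so the stated 92% power is not justified for the stimulation-by-moment interaction

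*Protocol article*

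**What the plan says.** The Protocol article, under Sample recruitment and selection, names gait velocity as the primary outcome and a two-way within-subject ANOVA as the test. Of the calculation it says "The sample size was calculated in G*Power software version 3.1, based on data from" the study cited as reference 35. The inputs are "alpha = 0.05; beta = 0.08; ηp^2^ = 0.43", and the result is "The sample size analysis indicates a minimum of 16 PwPD is required for this study". To allow for loss, 24 people are invited. The paragraph does not say which term of the ANOVA the 0.43 describes.

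The Introduction describes reference 35, which stimulated M1, as follows: "a single session of AE on the treadmill improved gait velocity and stride length, but these positive effects were not enhanced by tDCS application". The stated aim of the trial is to "investigate the acute effects of tDCS applied to different target areas combined with AE on the treadmill". Under Statistical analysis, the model is stimulation (four levels) by moment (pre, post), and the Bonferroni post hoc comparisons follow only if the two factors interact.

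**The concern.** Every session, sham included, contains the same 30-minute treadmill protocol. A pre-post gain common to all four sessions shows that people walk faster after exercise; it says nothing about tDCS. The tDCS question is whether the pre-post change differs between stimulation conditions. That is the interaction, and it also decides whether any post hoc comparison is made.

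A sample size for this question needs an effect size for that interaction. The protocol takes a very large one from a study it describes as showing no added benefit of tDCS. Either 0.43 belongs to a different term, or it conflicts with the Introduction's account of its source. In both cases the 92% power implied by beta 0.08 does not carry over to the comparison the trial is run to make. A reader of the results would still see a trial planned at 92% power.

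**Working it through.** **Inputs.** From the sample size paragraph: alpha 0.05; beta 0.08, so power 1 − 0.08 = 0.92; partial eta squared 0.43; N = 16, with 24 invited. From Statistical analysis: a 4 × 2 within-subject design, so the interaction has (4 − 1)(2 − 1) = 3 df and error df 3(N − 1). The number of measurements, correlation, epsilon and effect-size option entered in G*Power are not given, so several conventions were tried.

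**Effect size.** f² = 0.43 / (1 − 0.43) = 0.43 / 0.57 = 0.754, so f = 0.869.

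**Step 1: trying to reproduce 16.** Power is P(F′ > F crit), where F′ is noncentral F with df d and d(N − 1). The noncentrality is λ = f²·d·(N − 1) in the SPSS convention and λ = f²·d·N in the Cohen convention.

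| Term | Convention | Power at N = 16 | N for 0.92 | N for 0.80 |
|---|---|---|---|---|
| 1 df (such as pre-post) | SPSS | 0.881 | 18 | 14 |
| 1 df | Cohen | 0.900 | 18 | 13 |
| 3 df (4 × 2 interaction) | SPSS | 0.999 | 9 | 7 |

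The G*Power default option with correlation 0.5 gives 7 or fewer. None of these returns exactly 16 at power 0.92. The 1-df answer of 18 is close; the answer of 9 for the planned interaction is not.

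Other entries do land on or near 16, but each changes something:
- λ = f²·N with 3 df gives 16 at 80% power (0.806), not 92%.
- 0.43 entered as f with eight measurements gives 17 or 18 at 92%.
- 0.43 entered as f², with two measurements and zero correlation, gives 16 at 92%.

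The route to 16 cannot be identified from the article.

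**Step 2: can 0.43 be the interaction in reference 35?** For a fully within-subject term with d df, F = [ηp² / (1 − ηp²)] × [d(N − 1) / d] = 0.754 × (N − 1). Under sphericity, the smallest N at which this is significant at 0.05 is:
- 1 df: N = 9, F(1, 8) = 0.754 × 8 = 6.04, p = 0.040
- 2 df: N = 7, F(2, 12) = 0.754 × 6 = 4.53, p = 0.034
- 3 df: N = 6, F(3, 15) = 0.754 × 5 = 3.77, p = 0.034

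Unless that study was smaller than this, an interaction of 0.43 would have been reported as an enhancement by tDCS. The protocol reports the opposite.

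**Step 3: what the design can detect for the interaction.** The document gives no tDCS interaction effect, so the values below are assumptions (3 df, sphericity, SPSS convention).

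| Assumed ηp² | Power, 16 completers | Power, 24 completers |
|---|---|---|
| 0.20 | 0.78 | 0.94 |
| 0.14 | 0.57 | 0.79 |
| 0.10 | 0.41 | 0.61 |
| 0.06 | 0.24 | 0.37 |

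Solving for the effect, 80% power needs ηp² of about 0.21 with 16 or 0.14 with 24; 92% power needs about 0.27 or 0.19. Departure from sphericity lowers these powers: at ηp² 0.14 with epsilon 0.5 they are 0.39 and 0.57.

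**The case against.** The strongest reply is that a reader might infer two things the article does not support.

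The first is that 16 participants fail to deliver beta 0.08. This is not established. If 0.43 is accepted as the 3-df interaction, 16 gives power 0.999 in the SPSS convention. On a 1-df reading, 16 gives 0.88 to 0.90 and is only two participants short of 18. If all 24 invited complete, the 1-df power is about 0.98. A condensed article commonly omits the G*Power settings, so inexact reproduction is a reason to confirm the entry, not proof of an error. That 0.08 is a slip for 0.20 would be a guess.

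The second is that the text shows 0.43 to be the pre-post effect. It does not. No ANOVA term is named, and the source's sample size and F statistics are not given. It is a strong inference only.

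It is also fair to say that reference 35 concerned M1 alone. The Introduction cites favourable combined results for M1 with gait and balance training and for PFC with cycling, and says that simultaneous M1 and PFC stimulation with aerobic exercise is untested. A null interaction is therefore not the predicted result, and a large one is not excluded. Nor does the document say that a null result would be read as no effect.

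All of this stands, and it limits the point. It does not supply a justification for 0.43 as the interaction effect: the protocol drew that figure from reference 35, not from the favourable studies.

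**Conclusion.** The concern holds in a limited form: the stated 92% power is not justified for the stimulation-by-moment interaction, because its planning effect conflicts with the protocol's own description of the source. The most likely explanation is that 0.43 is the effect of moment, shared by all four sessions.

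The size depends on the true interaction, which the document does not give. At an assumed partial eta squared of 0.06, power is about 24% with 16 completers and 37% with 24, against the 92% implied. Only interactions of about 0.27 (16 completers) or 0.19 (24) would reach 92%. These figures assume sphericity and the SPSS definition of partial eta squared.

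Secondary point: 16 does not follow exactly from the stated inputs under the conventions tried with partial eta squared 0.43 at 92% power, so beta and the software settings need confirming. It would go too far to say that the trial misses its stated beta, or that the stated power does not exist.

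**What to change.** Revise the sample size paragraph as follows:

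- State which ANOVA term in reference 35 the 0.43 belongs to.
- Confirm or correct beta 0.08, and confirm the G*Power entry that led to 16 (number of measurements, correlation, epsilon, effect-size option).
- Do not claim 92% power for the stimulation-by-moment interaction on this basis.
- State what the design can detect for that interaction: with sphericity and SPSS partial eta squared, 80% power needs about 0.21 with 16 completers or 0.14 with 24, and at an assumed 0.06 power is about 24% or 37%.

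The cost is wording only. No extra participants, visits or analyses are needed. The one downside is a less favourable power statement. Reporting active-minus-sham differences with 95% confidence intervals would help readers, but that is optional reporting detail and not part of this correction.
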